Pregnancies complicated by midtrimester PPROM are associated with high immediate and long-term costs. These are caused by extended maternal hospital admissions, increased incidence of premature delivery, and frequent neonatal complications hereafter requiring NICU-admission.

Amnioinfusion might improve fetal outcome by preventing pulmonary hypoplasia, by preventing neurological complications, increasing time to delivery interval, and improving fetal biophysical profile through prevention of umbilical cord compression. It also might prevent fetal deformity [7]. Porat et al. [8] reviewed serial transabdominal amnioinfusion and meta-analysed observational as wel as randomised studies. The only two included randomised studies however were on women with PPROM between 24 and 34 weeks whereas the critical interval for development of pulmonary hypoplasia, the canalicular phase, exists between 16 and 28 weeks gestation. One quasi-randomised study included women with PPROM before 24 weeks. There were two observational studies on PPROM before 24 weeks. Recently, Roberts et al. [9] published the only randomized trial on PPROM between 16 and 24 weeks. They found no difference in the primary outcome (perinatal mortality 19/28 vs. 19/28; RR 1.0; 95% CI0.70-1.43), maternal or neonatal morbidity. The observed difference in long term outcome (4/28 morbidity free survival at 2 years in the treatment group vs 0/28 in the group with expectant management) justifies further study.

Adverse events after antepartum transabdominal amnioinfusion have been reported. It is not clear which adverse effects are to be attributed to the procedure rather than to the condition of PPROM and oligohydramnios, since conservatively managed PPROM carries high risks inherent to the condition itself [7]. Waters and Mercer recently reviewed perinatal mortality after conservatively managed PPROM <26 weeks [5]. Meta-analysis of 6 studies (n = 275) shows a perinatal mortality of 54%, (if restricted to <24 weeks this incidence is 57%). These data are biased by the fact that patients not amenable to continued expectant management were often excluded (i.e. stillbirths, pregnancy terminations), and therefore survival is likely to be overestimated.

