### Study parameters/endpoints

We will compare two groups:

1) Amnioinfusion for midtrimester PPROM with oligohydramnios, and

2) Expectant management for midtrimester PPROM with oligohydramnios.

The primary outcome measure will be perinatal mortality, defined as intrauterine death, intrapartum death or neonatal death in the first 28 days of life.

Secondary outcomes are:

• Gestational age at delivery.

• Time from membrane rupture to delivery.

• Indication for delivery.

• Successful amnioinfusion (defined as retention of infused fluid as defined by a single deepest pocket of amniotic fluid of more than 2 cm for at least 48 hours).

• Placental abruption.

• Cord prolapse.

• Chorioamnionitis, (defined as fever before or during labour as a temperature greater than 37.5°C on two occasion more than one hour apart or a temperature > 38.0°C with either uterine tenderness (or contractions), leucocytosis, maternal or fetal tachycardia, or a foul-smelling vaginal discharge in absence of any other cause of hyperpyrexia).

• Fetal trauma due to puncture.

• Maternal length of stay in hospital.

Occurrence of secondary outcomes placental abruption, cord prolapse, chorioamnionitis and fetal trauma will be related to the number of amnioinfusions that have been performed.

Neonatal endpoints:

• Lethal pulmonary hypoplasia diagnosed according to radiological, clinical and pathological criteria. Pathological criteria are based on radial alveolar counts and lung/body weight ratios according to Askenazi and Perlman [11], when radial alveolar counts cannot be obtained, criteria by Wigglesworth et al. will be used [12]. Clinical criteria used to diagnose lethal pulmonary hypoplasia are: immediate onset of severe respiratory insufficiency after birth, small lung capacity and requirement of high ventilatory pressures in the absence of obstruction or atelectasis. Radiological criteria according to Leonidas will be used [13].

• Non-lethal pulmonary hypoplasia diagnosed using same clinical and radiological criteria in surviving neonates.

• Survival till discharge from NICU.

• Neonatal mortality, defined as neonatal death in the first 28 days of life.

• Chronic lung disease (CLD), CLD defined as oxygen dependency at 28 days of life [14].

• Number of days on ventilatory support.

• Length of stay in hospital.

• Necrotising enterocolitis (NEC) more than stage I and defined according to the criteria of Bell et al. [15].

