### Statistical analysis

The analysis of the randomised clinical trial will be performed on an intention-to-treat principle. The differences between the amnioinfusion and expectant management will be assessed by calculating the ratio of the outcome rates in the two groups. Hence, the measure of association is a relative risk (RR) with a 95% confidence interval (CI), calculated using a log-binomial model. Time to delivery will be evaluated by Cox proportional hazard analysis, Kaplan-Meier estimates and tested with a log rank test.

In case of equivalence between outcomes, the analysis will be repeated on an “as-treated” basis. Subsequently, primary and secondary outcomes will be described in a subgroup of women with successful amnioinfusion (retention of infused fluid first 48 hours). All analyses will be adjusted for the fact that an interim analysis will be performed using the O’Brien-Flemming alpha spending function [18]. Consequently, a nominal P value of less than 0.049 will be considered to indicate statistical significance.

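### The as-treated repeat is triggered by an undefined equivalence that a superiority trial of 28 per arm cannot show, so in practice an inconclusive ITT result would trigger it

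*Protocol article*

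**What the plan says.** All of this is in the protocol article.

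- **Primary analysis** (Statistical analysis): "The analysis of the randomised clinical trial will be performed on an intention-to-treat principle". The abstract makes the same commitment. The effect measure is fixed too: "the measure of association is a relative risk (RR) with a 95% confidence interval (CI), calculated using a log-binomial model".
- **Conditional repeat** (same section): "In case of equivalence between outcomes, the analysis will be repeated on an" as-treated basis. No margin and no equivalence test are given.
- **Subgroup** (next sentence): "Subsequently, primary and secondary outcomes will be described in a subgroup of women with successful amnioinfusion (retention of infused fluid first 48 hours"). Study parameters/endpoints defines success as "retention of infused fluid as defined by a single deepest pocket of amniotic fluid of more than 2 cm for at least 48 hours".
- **Decision rule**: after allowance for the interim look, which the section applies to all analyses, "a nominal P value of less than 0.049 will be considered to indicate statistical significance".
- **Design** (Sample size calculation): mortality of 70% reduced to 35%, two-sided α 0.05, β 0.20, 28 women per arm.
- **A trial of the same size** (Background): "perinatal mortality 19/28 vs. 19/28; RR 1.0; 95% CI0.70-1.43".

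**The concern.** Equivalence is a positive claim. It needs a margin set in advance and an interval narrow enough to lie inside it, and this trial has neither. The only decision rule in the text is the 0.049 threshold, so failing to reach it is the only reading that makes the trigger operational. On any other reading, someone must judge after seeing the data whether the arms look alike.

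Two things are at stake. First, an inconclusive result could be reported as equivalence when a large benefit or harm remains possible. Second, the follow-on analyses leave the randomised comparison, and the protocol's own text gives reasons to expect a direction:

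- Infusion needs an identifiable fluid pocket (Interventions), and fetal loss and delivery end the intervention (Safety reporting). Allocated women who are never infused may therefore tend to have the worst prognosis.
- Success requires the pregnancy to continue and fluid to be retained for 48 hours after an infusion, which cannot occur in the control arm. The trial's rationale is that lack of fluid harms the fetal lung, so retention is plausibly prognostic.

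**Working it through.** **1. The plan's own figures.** Sample size, unpooled formula: (1.960 + 0.842)² × (0.7×0.3 + 0.35×0.65) / 0.35² = 7.849 × 0.4375 / 0.1225 = 28.03 per arm. The stated 28 reproduces and is not in dispute.

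Interval for 19/28 v 19/28: SE(log RR) = √[2 × (1/19 − 1/28)] = 0.184, and exp(±1.96 × 0.184) gives 0.70 to 1.43, as the Background states. On the risk-difference scale this is ±24.5 percentage points.

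**2. What a non-significant result could contain** (uncorrected chi-square):

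| Deaths, control v infusion | RR (95% CI) | p |
|---|---|---|
| 20/28 v 20/28 | 1.00 (0.72–1.39) | 1.00 |
| 20/28 v 14/28 | 0.70 (0.45–1.09) | 0.10 |
| 20/28 v 13/28 | 0.65 (0.41–1.03) | 0.057 |

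The last row is a 25-point reduction (7/28) and would still fall on the equivalence side of the rule.

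**3. What equivalence would need.** Two one-sided tests at 0.05, 80% power, 70% mortality in both arms: n per arm = (1.645 + 1.282)² × 2 × 0.21 / margin². For assumed margins of 10, 15 and 20 points this gives 360, 160 and 90 per arm.

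**4. How often the trigger would fire on this reading.** Exact enumeration of the chi-square at 0.049 with 28 per arm, interim look ignored: 25% if the truth is 70% v 35%, 54% for 70% v 45%, 67% for 70% v 50%, 88% for 70% v 60%. Only the first pair is in the protocol. The others are assumptions.

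**5. As-treated repeat with no treatment effect.** Assume 70% mortality in both arms (19.6 expected deaths of 28), k women allocated to infusion who lose the pregnancy before any infusion and are counted with controls, and no crossover. Mortality is (19.6 − k)/(28 − k) among the infused and (19.6 + k)/(28 + k) in the other group.

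- k = 3: 16.6/25 = 66.4% v 22.6/31 = 72.9%, RR 0.91.
- k = 5: 14.6/23 = 63.5% v 24.6/33 = 74.5%, RR 0.85.
- k = 0: RR 1.00, because as-treated and ITT are then the same analysis.

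In a simulation of 200,000 null trials per scenario, the chance of a nominally significant as-treated result favouring infusion, after a non-significant ITT result, was 0%, 5.0% and 15.3% for early-loss probabilities of 0, 10% and 20%.

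**6. Successful-infusion subgroup with no treatment effect.** Assume 50% of the infusion arm retain fluid and 70% mortality overall. If the odds ratio of death for retainers v non-retainers is 0.5, 0.33 or 0.25, mortality among retainers is 62.8%, 58.8% or 56.3%. Set against 70% in all controls, the RR is 0.90, 0.84 or 0.80. The retention share, the odds ratios and the contrast itself are assumptions.

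**The case against.** The strongest defence is that nothing primary is touched. ITT is the analysis, the as-treated run is a repeat of it, and the RR with its interval is already required, so a reader would see how wide a null result is. Both follow-on analyses are pre-specified, so they are not post hoc. All of that stands, and it limits the damage to how a null result is interpreted.

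Several stronger readings are tempting but not supported:

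- *That the protocol equates non-significance with equivalence.* It does not say so. This is an inference, drawn because no other criterion is given.
- *That both follow-on analyses favour amnioinfusion whatever happens.* For as-treated this is conditional. The article does not say how uninfused women are classified, and a full protocol or SAP may. Without non-adherence or crossover there is no bias, and selective crossover could reverse it. Eligibility also works against very early loss, since women with contractions, infection, cervical change or fetal distress are excluded and randomisation comes at least 72 hours after diagnosis.
- *That the plan compares successful infusions with controls.* It says only that outcomes are described, and names no comparator. Whether the subgroup depends on the trigger at all rests on the word *Subsequently*.
- *That a null result is the likely outcome.* Under the planned effect its chance is about 25%. Higher figures need a smaller assumed effect.

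What the defence does not answer is the rule itself. A stated trigger that the design cannot meet is a fault in the text, not missing detail. The repeat is not labelled exploratory, and the 0.049 threshold is written to cover all analyses.

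**Conclusion.** The point holds in a limited form. The protocol makes an as-treated repeat conditional on an equivalence that it does not define and cannot demonstrate with 28 per arm. In practice the condition would be a non-significant ITT result, which is inconclusive. The primary test, its error rate and the sample size are unaffected.

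The inability to show equivalence rests on the protocol's own numbers (0.70 to 1.43 with identical counts). The size of the as-treated bias (RR about 0.91 or 0.85 with no effect) rests on assumed early losses of 3 or 5 of 28, counted as controls. The documents give no figure for this, and the bias can be zero or reversed. A contrast of successful infusions with all controls would be expected to favour amnioinfusion, but the text does not commit to one.

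**What to change.** 1. Delete the equivalence trigger. State that a non-significant ITT result is inconclusive and is interpreted from its RR and confidence interval.
2. If an effect of treatment received is wanted, pre-specify it whatever the ITT result and label it exploratory. Estimate it with randomisation as the instrument (complier average causal effect, CACE) instead of as-treated.
3. Limit the successful-infusion subgroup to description within the amnioinfusion arm, with no contrast or significance test against controls.

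A landmark at 72 hours based on the single deepest pocket in both arms is not a good substitute. The infusion directly changes that measurement. The Interventions section also times it differently in the two arms: 48–72 hours after the first infusion in one, at twice-weekly visits in the other.

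The cost is a change of wording and the loss of the simple as-treated contrast. The CACE will be imprecise. On the risk-difference scale it is the ITT difference divided by the proportion infused, if no control is infused. With identical counts of 19/28 and 25 or 23 of 28 infused, the ±24.5-point interval widens to about ±27 (24.5 × 28/25) or ±30 (24.5 × 28/23). The estimate itself stays at zero when the ITT difference is zero.

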## Discussion

There are signs that pregnancies complicated by oligohydramnios after midtrimester PPROM might benefit from amnioinfusion. However, currently there is insufficient evidence to recommend this procedure. The benefits might be increased neonatal survival and decreased pulmonary complications, especially pulmonary hypoplasia. Potential harms include placental abruption, premature labour and delivery, cord prolapse, chorioamnionitis, fetal loss, fetal trauma due to puncture. Of these, only the last mentioned is not a known potential complication of the underlying condition itself as well (midtrimester PPROM). Expectant management indeed carries these same risks. At present, there is no evidence on which a rational choice between expectant management or therapeutic amnioifusion can be based.

## Abbreviations

3D: 3-dimensional; AC: Abdominal circumference; AE: Adverse event; BPD: Bronchopulmonary dysplasia; CCU: Cardiac care unit; CLD: Chronic lung disease; CRP: C-reactive protein; CTG: Cardiotocography; DSMB: Data Safety Monitoring Board; FL: Femur length; GA: Gestational age; IRDS: Infant respiratory distress syndrome; IVH: Intraventricular haemorrhage; METC: Medical research ethics committee (MREC); in Dutch: medisch ethische toetsingscommissie (METC); NEC: Necrotizing enterocolitis; NICU: Neonatal Intensive Care Unit; PPROM: Preterm prelabour rupture of membranes; PVL: Periventricular leucomalacia; SAE: Serious adverse event; SDP: Single deepest pocket (amniotic fluid); TC: Thoracic circumference; US: Ultrasound; WMO: Medical Research Involving Human Subjects Act (Wet Medisch-wetenschappelijk Onderzoek met Mensen).
